## Abstract

**Background:**

Obesity is of major pathogenetic importance to type 2 diabetes, it contributes to poor glycemic control and increases the risk of cardiovascular disease. Over 80% of patients with diabetes type 2 are overweight. To achieve a more favourable risk profile, changes in diet and lifestyle are needed. However, current treatment programs for obese DM type 2 patients are not effective in the long term. In this RCT, we compare the effectiveness of a Combined Psychological Intervention (CPI) and usual care in maintaining the favourable effects on weight and risk profile during 2 years of follow-up after a Very Low Calorie Diet (VLCD).

**Methods and design:**

In a randomised parallel group intervention study, 140 patients with type 2 diabetes and overweight (BMI>27 kg/m2) will be recruited from the outpatient department of the Erasmus Medical Centre.

After obtaining ≥5% of weight loss with a VLCD, participants will be randomly assigned to CPI or usual care for 10 weeks. CPI consists of cognitive behaviour therapy, problem solving therapy and proactive coping.

Primary outcome measure is weight change (kg).

Other outcome measures are Body Mass Index (BMI = weight (kg)/length (m)2), waist circumference (cm), systolic blood pressure (mmHg), HbA1c (mmol/mol), lipid levels (LDL, HDL, TG (mmol/l) and chol/HDL-ratio), antidiabetic agents and doses, cardiovascular risk profile (UKPDS), lifestyle and quality of life (EuroQol EQ-5D). Psychosocial parameters are also studied, as secondary outcomes as well as determinants for weight loss.

When successful, we want to conduct an analysis of the cost effectiveness of the intervention as compared to usual care.

**Discussion:**

We expect that a CPI after a VLCD will be effective in maintaining weight loss and improving cardiovascular risk and glycaemic control, while being cost-effective and improving quality of life in patients with type 2 diabetes.

**Clinical trials registration:**

trialregister.nl NTR2264

## Background

Diabetes has become a worldwide epidemic: the estimated global prevalence was 2,8% in 2000 and is expected to rise up to 4,4% in 2030. In the year 2000 the excess global mortality attributable to diabetes was 5,2% making diabetes the fifth leading cause of death [1]. The increase in prevalence is associated with aging of the population, the increasing prevalence of obesity in combination with physical inactivity. Cardiovascular disease is the major cause of death among patients with diabetes. An intensive pharmaceutical and behavioral therapy treatment has been estimated to reduce the risk of cardiovascular and micro vascular events by approximately 50% [2].

Approximately 80% of the people with type 2 diabetes are overweight. Losing weight is the cornerstone of prevention and treatment of type 2 diabetes: it decreases the resistance to insulin, improves glycaemic control and reduces hypertension and lipid abnormalities [3-5]. Weight loss interventions thus may contribute to a reduction of cardiovascular risk and is shown to reduce mortality in patients with type 2 diabetes and obesity [6].

Unfortunately, interventions aimed at weight reduction have only a limited effect in the long run because of regain of the initial weight loss. The required long-term lifestyle change seems difficult to achieve [7]. A meta-analysis of weight loss interventions in adults with type 2 diabetes showed that multi-component interventions including Very Low Calorie Diets may hold promise for achieving weight loss [7,8]. However, trials with long follow-up periods are lacking and the most effective type of psychological intervention remains unclear.

In the present study, we determine the effect of an integrated multi-model cognitive group therapy, in obtaining and maintaining favourable effects on weight and cardiovascular risk profile during 2 years of follow-up after a Very Low Calorie Diet.

### Very Low calorie diet

A Very Low Calorie Diet (VLCD) is a diet of less than 800 kilocalories (kcal) daily [4]. The very low intake of fat and carbohydrates, but normal amount of proteins (0,8 g/kg ideal bodyweight per day) enhances lipolysis and ketosis while preventing a negative nitrogen balance, sparing lean body mass [9].

The most commonly used VLCD’s are commercially available mixed-formula diets, containing various amounts of carbohydrate, fat and high quality protein, and have proven safety for use in patients with type 2 diabetes [9,10].

The short-term effects (i.e. < 6 months) of a VLCD in overweight patients with type 2 diabetes are favourable on weight, glycaemic control, hypertension and dyslipidaemia [11-15]. However, study outcomes are less positive in the long term (i.e. > 1 year follow-up): patients regain most of the lost weight and HbA1c returns to the same value as prior to the intervention. Nonetheless, participants often needed less anti-diabetic agents [16-18]. The study of Jazet, et al. [19] seems to be a positive exception: 18 months after a 30-day VLCD period, favourable effects on weight, blood pressure and dyslipidaemia were maintained in 18 obese patients with diabetes type 2, but with no effect on HbA1c. The authors indicated that the success was based on the strong motivation of the patients to prevent a need for insulin and a slow reintroduction of normal diet. Limitations of this study, however, were the small intervention group and the lack of a control group.

Taken together, randomized controlled trials of sufficient duration focused on prevention of weight gain after a VLCD in DM type 2 patients are required to improve the effectiveness of VLCDs.

### Weight maintenance

To achieve weight maintenance after successful weight loss, a permanent behaviour change is needed. For this purpose, a variety of psychological interventions have been implemented in weight reduction programmes. Behaviour therapy and cognitive behaviour therapy (CBT) are potential psychological interventions facilitating better maintenance of weight loss [20]. CBT is used to describe a wide range of techniques to change thinking patterns and behaviours. As a result, interventions are heterogeneous and the findings are difficult to compare.

We identified three promising psychological interventions to attain better results in sustaining weight loss: cognitive (behaviour) therapy, problem solving therapy and proactive coping. In the current study, we propose to combine them into an integrated weight maintenance programme.

### Cognitive behaviour therapy

Within cognitive psychology, humans are regarded as information processing systems, where knowledge is organized in so-called schemas. Cognitive schemas are activated by incoming information, leading to cognitions (thoughts), emotions and subsequently to behaviour. According to the founding father of the cognitive therapy, Aaron Beck, emotional disorders such as depression and anxiety disorders result from dysfunctional schemas. Cognitive therapy focuses on changing dysfunctional schemas and cognitions, using behavioral experiments and challenges [21]. In eating disorders, the cognitive model was first used to treat bulimia nervosa by adjusting overvaluation of weight and shape based on low self-esteem [22,23]. In the treatment of obesity, this model is combined with the cognitive model for addiction, which is based on the assumption that addictive behaviour is enhanced by dysfunctional cognitions during exposure to external stimuli like the smell or sight of food [24].

In a Cochrane review [20] concerning the effect of psychological interventions in the treatment of overweight and obese patients, positive effects of cognitive behaviour treatment on weight loss were described, particularly when combined with diet and/or physical activity. In a number of studies, weight loss was enhanced significantly by the addition of the cognitive component to an intervention of diet and/or exercise [25-28]. Moreover, it was found that a longer duration of the intervention and more frequent clinical contact was associated with an increased effect. However, studies with substantial follow-up (i.e. > 1 year) are lacking.

In patients with type 2 diabetes, psychotherapy (especially CBT) improves glycaemic control (HbA1c −1,0%) and psychological well-being [29]. Surprisingly, CBT did not appear to affect weight control in this patient group. Perhaps this was caused by too short duration of the studies (i.e. <6 months), as CBT may encourage long-term behavioral changes [29].

### Problem solving therapy

Problem Solving Therapy (PST) is defined as the self-directed cognitive-behavioral process by which a person attempts to identify effective or adaptive solutions for specific problems encountered in everyday living [30,31]. PST is recognized as an effective treatment of depression [32,33]. The problem-solving model for obesity treatment was first described by Perri, Nezu and Viegener in 1992 [34] and proposes that active problem solving efforts by a health care provider can help the obese person encounter everyday problems in their weight management. Perri, et al. found significantly greater long-term weight reductions in participants, who completed a PST-intervention, compared to participants receiving behavioral therapy [35]. Moreover, a recent study showed that people with better problem-solving skills lost more weight and were more compliant to therapy [36].

### Proactive coping

Proactive coping (PC), directed at an upcoming instead of an ongoing stressor, is a new focus in positive psychology research. PC consists of efforts undertaken in advance of a potentially stressful event to prevent it or modify its form before it occurs. The theory described by Aspinwall and Taylor consists of five stages: PC starts with the ‘accumulation of resources’ such as time, money, planning or organizational skills and social support, so that one is prepared as much as possible to deal with future threats. ‘Recognition’ refers to the ability to see a potential stressful event coming, followed by ‘initial appraisal’ (what is this and should I be worried about this?). The next stage consists of ‘initial coping efforts’: activities undertaken to prevent or minimize a recognized or suspected stressor. Finally, the ‘use of feedback’ involves the evaluation of the stressful event itself and the effects of one’s preliminary efforts [37].

Schwarzer and Taubert described PC as a way of aspiring a positive future by accumulating resources and realistic goal setting [38]. A recent publication has shown that the pursuit of goals was related to improved wellbeing, while preventing a negative future was not [39].

A study of the effects of PC on the self-care behaviours of newly diagnosed DM patients revealed that the treatment was highly appreciated and even after 9 months improvements in eating and exercising habits were seen. In addition, the intervention was effective in reducing both weight and blood pressure after 9 months, but had no effect on HbA1_c_ or lipid profile [40].

In the current randomized study, we compare the effect of a Combined Psychological Intervention (CPI) with usual care on weight maintenance after a Very Low Calorie Diet. Hence, we do not compare the effectiveness of Cognitive Behaviour Therapy with neither Problem Solving Therapy nor Proactive Coping, but combine these three therapies into an integrated multi-model program.

### Objectives

The primary objective of this study is to determine if an integrated multi-model cognitive group therapy, is more effective in preventing weight regain after a Very Low Calorie Diet compared to usual care.

The secondary objectives are to investigate whether an integrated multi-model cognitive group therapy following a VLCD has an effect on glycaemic control, cardiovascular risk profile, psychological variables and quality of life, and subsequently to determine which patient group benefits most of the intervention.

The tertiary objective is to determine whether the intervention is cost-effective.

### Ethical approval

This research is approved by the Medical Ethics Committee of the Erasmus Medical Centre in Rotterdam (reference number MEC-2009-143/NL26508.078.09), in compliance with the Helsinki Declaration.

## Methods/design

### Design of the study

This study is a randomized controlled parallel group intervention trial.

When patients lose equally or more than 5% of their bodyweight in the first 8 weeks of the VLCD, they are included in the intervention trial testing CPI. This arbitrary cut-off value was chosen because of its relatively large effect on the risk profile [3]. Moreover, we need a relevant weight loss to investigate weight maintenance after weight reduction. After randomization, stratified to the achieved weight loss at 8 weeks, participants are assigned to one of the following conditions:

1. VLCD + conventional treatment

2. VLCD + conventional treatment + CPI

The duration of the diet period will be 20 weeks: 8 weeks of VLCD (<800 kcal/day) followed by 12 weeks of slowly reintroducing a normal, mildly energy-restricted diet (1300 kcal/day). During week 10 of the diet, the intervention group starts with a total of 17 sessions of CPI. The first 10 sessions are weekly sessions; followed by two 2-weekly sessions, two monthly sessions, two 3-monthly sessions and 1 session with an interval of 6 months.

Outcome measurements are assessed at baseline, after finishing the intensive CPI-period at 4 months and subsequently at 1 year, 1,5 years and 2 years after randomization. At 8 weeks (randomization after VLCD), only the primary outcome (weight) will be measured.

Figure 1 shows the design of the study.

**Figure 1 F1:**
[figure not shown]
**Flow chart of participants.** VLCD = Very Low Calorie Diet; CPI = Combined Psychological Intervention.

The study started in may 2010 with a pilot and inclusion will be completed in 2013. The follow-up will continue until 2015.

### Study population

Patients are recruited from the outpatient diabetes clinic of the Erasmus Medical Centre in Rotterdam by the medical team, based on the in- and exclusion criteria shown in Table 1. In our hospital, a tertiary referral centre, we see both patients with only oral antidiabetic agents and patients treated with one or more insulin doses daily. In general, our patients will have more complex disease and more comorbidity compared to the average diabetic patient referred to a GP. How ever, GP’s can also directly refer their eligible patients to our trial. Patients interested in participating in the study will receive an information letter and a questionnaire to be filled in at home. Two weeks later they will visit the outpatient clinic for an intake interview with the researcher ([name]). Eligibility will be checked again. After signing the informed consent form by the patient, the baseline measurements will be performed.

**Table 1 T1:** Eligibility

Inclusion criteria:	
**1**	Diagnosed diabetes mellitus type 2
**2**	Age 18–75 years
**3**	BMI ≥ 27 kg/m^2^
Exclusion criteria:	
**6**	Pregnancy or lactation during the study
**7**	Inadequate expression of the Dutch language (spoken and written)
**8**	Inability to lose ≥ 5% of bodyweight during the first 8 weeks of VLCD
**9**	Severe psychiatric problems
**10**	Significant cardiac arrhythmias, unstable angina, decompensated congestive heart failure, major organ system failure, untreated hypothyroidism and/or myocardial infarction, end-stage renal disease, cerebrovascular accident or major surgery in the last 3 months.

Patients with psychiatric disorders or major psychological disturbances are excluded from the trial. Patients with eating disorders (bulimia nervosa and binge eating disorder) or depression are not excluded, since it is expected that these conditions are common among patients with type 2 diabetes and previous research has shown that cognitive behaviour therapy can have beneficial effects in these patient groups [28,41-43]. We will analyze the effect of these background variables on the outcome of the intervention.

### Randomization

Groups of 20 patients will start with a VLCD concomitantly. After 8 weeks of VLCD, the patients who lost ≥5% of bodyweight are randomly assigned to either or the intervention group (usual care + CPI) or the control group (usual care) with an allocation ratio of 1:1. The stratified randomization is computer controlled, carried out by a secretary and supervised by a statistician, who are both not involved in the trial. The reason for a stratified randomization is to avoid an unsuccessful randomization with regard to weight loss during the VLCD. It is not possible to correct afterwards in the analysis, as it is the primary outcome measurement. We defined the following strata (based on clinical experience):

1. 5% - 7,5%

2. 7,5% - 10%

3. >10% weight loss after 8 weeks of VLCD.

The statistician generates the allocation sequence and hands it over to the secretary of the department of Medical Psychology and Psychotherapy, who is not involved in the study, to guarantee allocation concealment. The secretary assigns the participants to their group and makes a list for [name], who will plan their study appointments.

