### Sample size calculation

After randomization of 75 participants, the sample size calculation was carried out by an independent statistician to base it on realistic data.

Sample size was calculated with SPSS 17.0, using the mixed-model ANOVA procedure described by Aberson [44].

Alpha was set at 0.05, power at 0.80 and the baseline-end correlation at 0.90. A clinically relevant difference between the treatment groups is 5% weight loss [3]. Mean weight at the start of the treatment is about 110 kg, with a standard deviation of 22, this equals an effect size of d = 0.25.[45] With this power calculation we estimate that we need 52 patients in each group. Anticipating a dropout rate of 25%, we aim for a total sample size of 140.

For the most important secondary outcomes we calculated the detectable difference with the sample size of n=104, alpha 0.05 and power 0.80 (Table 2). The detectable differences are quite small, so the aimed sample size seems adequate to analyse at least these secondary outcomes.

**Table 2 T2:** Power calculation secondary outcomes

**Secondary outcome:**	**SD:**	**Detectable difference:(n = 104, β=0.8 α=0.05)**
Waist circumference	11	2.75 cm
Blood pressure sys/dias	20/20	5/5 mmHg
Total cholesterol	1.4	0.35 mmol/l
LDL cholesterol	1.0	0.25 mmol/l
HDL cholesterol	0.7	0.2 mmol/l
Triglyceride	3.0	0.75 mmol/l
HbA1c	12	3 mmol/mol
Insulin	50	12.5 IU
Depression (HADS score 0–21)	3	0.75
Anxiety (HADS score 0–21)	4	1.0
Self esteem (RSE score 10–40)	5	1.25
Fatigue (CIS score 8–56)	13	3.25
Concentration (CIS score 5–35)	8.5	2.1
Motivation (CIS score 4–28)	6	1.5
Activity (CIS score 3–21)	5	1.25
Quality of life (EuroQol 5D score 1–3)	0.5	0.125
Quality of life (EuroQol VAS 1–100)	21	5.25

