### Interventions

#### Phase 0: very Low calorie diet

The first part of the study (before randomization) is the same for all participants and consists of a Very Low Calorie Diet (VLCD) for the duration of 8 weeks, with a phase-out of 12 weeks. When after 8 weeks of VLCD a loss of 5% or more of the initial bodyweight is reached, random allocation to the intervention- and control group will take place. Patients losing less then 5% of bodyweight in the first 8 weeks are excluded from the study and will receive usual care, including dietary advice.

The use of a VLCD is an integrated part of the dietary treatment at our outpatient diabetes clinic. Normally, the patients are free to choose between the different types of weight reduction strategies. In the present study however, only one type of weight reduction therapy is used (VLCD).

The product we use for this study is Glucerna SR®, a product specifically developed for patients with diabetes and based on a combination of slow released carbohydrates, a low-fat, high monounsaturated fatty acid content and the addition of dietary fibre. Various studies indicate that this product decreases the postprandial blood glucose levels, which may have a lowering effect on HbA1c. This diabetes-specific diet product is also used as a meal replacement for achieving weight reduction in people with type 2 diabetes, with positive effects on weight control, glycaemic control and lipid profile [46-48]. We have chosen to use a twice a day regimen of meal replacements, together with a small dinner, providing 750 kcal, 67 g carbohydrates, 54 g protein and 32 g fat (of which 16 g monounsaturated fatty acids (MUFA)) a day and RDA recommendations in micronutrients. We believe that enabling the participants to have dinner with their family during the VLCD will improve compliance.

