#### Primary outcome

The primary endpoint with respect to the efficacy of CPI is the differential course of weight (kg) between both study groups, measured at 8 weeks and at 2 years follow-up. Weight is measured to the nearest 0.1 kg, after removal of shoes using a Seca 888 compact digital flat scale.

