### Statistical analyses

All analyses will be conducted according to the intention-to-treat as well as the on-treatment principle. We consider participants on-treatment when they miss less then 8 sessions CPI.

At baseline, comparability between the control- and intervention group will be assessed to test the success of the randomization. As measures of central tendency for numerical data we will use the mean (in case of normal distribution) and median values (in case of non-normal distribution), with respectively the standard deviation and interquartile range as measures of dispersion.

Mixed modelling, also known as random effect modelling, multilevel or hierarchical linear regression analyses will be applied for longitudinal analyses of the data. Mixed modelling can efficiently handle data with missing and unbalanced time-points. It corrects for bias when absence of data is dependent on characteristics that are present in the models (missing at random, MAR) [62]. There will be two levels in the models. The patients constitute the upper level, their repeated measures the lower level. First, for each outcome variable a saturated model will be postulated, with the primary or secondary outcomes as dependent variables. The saturated models will include treatment group, time, quadratic time, logarithm of time and all treatment-time interactions as fixed effects. The deviance statistic [63] using restricted maximum likelihood [64] will be applied to determine the covariance structure. Next, using Wald tests, the saturated models will be reduced by eliminating insignificant fixed effects. The significance of the difference between the saturated models and the parsimonious final models will be determined with the deviance statistics using ordinary likelihood.

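### The protocol wrongly rules out any adjustment for weight loss during the VLCD, and its listed model omits this stratification factor; the possible cost is precision, not bias

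*Protocol article*

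**What the plan says.** Protocol article, Design of the study: "After randomization, stratified to the achieved weight loss at 8 weeks, participants are assigned to one of the following conditions". The Randomization section defines three strata of percentage loss (5 to 7.5, 7.5 to 10, above 10) and gives the motive: "The reason for a stratified randomization is to avoid an unsuccessful randomization with regard to weight loss during the VLCD". It then adds: "It is not possible to correct afterwards in the analysis, as it is the primary outcome measurement".

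On timing, the section on Phase 0 says of the VLCD: "The first part of the study (before randomization) is the same for all participants". The Primary outcome section defines the endpoint as "the differential course of weight (kg) between both study groups, measured at 8 weeks and at 2 years follow-up".

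The Statistical analyses section postulates one saturated mixed model for each outcome variable, primary or secondary: "The saturated models will include treatment group, time, quadratic time, logarithm of time and all treatment-time interactions as fixed effects". Fixed effects that are not significant on Wald tests are then removed. Stratum, VLCD weight loss and pre-VLCD weight are not in the list.

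**The concern.** The sentence treats weight loss during the VLCD as if it were the primary outcome. On the protocol's own definitions the VLCD loss ends at week 8, where the primary outcome begins. A quantity fixed before allocation can be a covariate, and one used to stratify would normally be carried into the analysis.

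Precision is at stake. Stratified allocation makes the arms alike on the factor, which reduces the true sampling variability of the treatment contrast if the factor is prognostic. A model that ignores the factor leaves its variance in the residual, so the reported standard error does not show that reduction. Confidence intervals are then too wide, the test rejects too rarely under the null, and some power is given up.

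This is more than detail left to a fuller document. The protocol declares the adjustment impossible and also gives an explicit list of fixed effects without it, so an analysis plan written to agree with it would carry the error forward.

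**Working it through.** **1. Which quantity is which.**
- VLCD loss: pre-VLCD weight to week 8, expressed as a percentage. It is complete before allocation.
- Primary outcome: course of weight from week 8 to 2 years.
- Overlap: the 8-week weight enters both, as the end of the first and the start of the second.
- Secondary outcomes: Design of the study says that only weight is measured at 8 weeks, so the other outcomes have the pre-VLCD visit as their starting value. BMI aside, they are not computed from weight, so the reason given for not adjusting has no bearing on them.

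**2. The plan's own sample size.** Inputs are from the Sample size calculation section: "Alpha was set at 0.05, power at 0.80 and the baseline-end correlation at 0.90"; SD 22 kg; mean weight 110 kg; and "A clinically relevant difference between the treatment groups is 5% weight loss", that is 0.05 × 110 = 5.5 kg. Sidedness is not stated; two-sided is assumed.
- With two time points the group-by-time test is a comparison of change scores. SD of change = 22 × √(2 × (1 − 0.90)) = 9.84 kg.
- The normal approximation gives 51 per arm. With the noncentral t, 51 gives power 0.798 and 52 gives 0.806, so 52 per arm reproduces.
- 104 / (1 − 0.25) = 139, or 70 per arm = 140. This also reproduces. The sample size is not at fault.

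**3. Effect of leaving the stratum out.** R2 is the share of the variance of the 8-week-to-2-year change that the strata explain. The documents do not give it, so a range is assumed.
- SE as reported without the stratum: 9.84 × √(2/52) = 1.93 kg. Standardised effect z = 5.5 / 1.93 = 2.85.
- True SE under balanced strata: 1.93 × √(1 − R2).
- SE overstatement: 1/√(1 − R2) − 1.
- Type I error without the stratum: 2 × (1 − Φ(1.96/√(1 − R2))).
- Power without the stratum: Φ((2.85 − 1.96)/√(1 − R2)). Power with it: Φ(2.85/√(1 − R2) − 1.96).

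| Assumed R2 | SE overstated by | Type I error, stratum omitted | Power, omitted | Power, included |
|---|---|---|---|---|
| 0 | 0% | 5.0% | 0.81 | 0.81 |
| 0.05 | 2.6% | 4.4% | 0.82 | 0.83 |
| 0.10 | 5.4% | 3.9% | 0.83 | 0.85 |
| 0.15 | 8.5% | 3.4% | 0.83 | 0.87 |

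The gain in power is about 1, 3 and 4 points at R2 of 0.05, 0.10 and 0.15. The type I figures apply to the part of VLCD loss that the three strata capture, since only that part is balanced by the randomisation.

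**4. Simulation check.** 104 patients, stratified 1:1 allocation, stratum shares assumed at 40/35/25%, 6,000 runs per scenario. At R2 = 0.20 the mean SE was 1.93 kg without the stratum and 1.72 kg with it, type I error about 3% against 5%, and power about 84% against 89%. The treatment estimate was unbiased in both analyses.

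**5. Which term produces the gain.** If 8-week weight is one of the repeated responses, the treatment effect is the treatment-by-time term, a within-patient contrast. A stratum main effect shifts a patient's weights equally at both times and cancels out of that contrast. A simulation of the two-time-point random-intercept model (52 per arm, R2 0.15) gave these mean SEs for treatment-by-time: 1.923 kg with no stratum, 1.923 kg with a stratum main effect, and 1.768 kg with stratum-by-time.

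**The case against.** **The sentence has a defensible core.** VLCD loss is computed from the 8-week weight, which is the first value of the primary outcome. If the sponsor meant that a response value cannot also be a covariate in the same model, that is correct. It does not bar the stratum, stratum-by-time terms or pre-VLCD weight, and it does not reach the secondary outcomes. The sentence as written is too broad.

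**The harm is conditional and modest.** This stands. It depends on an R2 that the documents do not give, it errs on the conservative side, and the planned 80% power is met at 52 per arm without adjustment.

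**Covariates are often completed in an analysis plan.** This would answer silence. It does not answer a statement that adjustment is impossible.

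**Inferences the documents do not support.** A reader might infer that the sentence caused the omission from the model; the Statistical analyses section gives no reason for its list, so that link is conjecture. A reader might also think that adding VLCD loss and 8-week weight as plain covariates is a one-line repair. With 8-week weight kept as a response, the first gives no gain for the primary contrast and the second would use one value as both response and covariate.

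**Conclusion.** The point holds in a limited form. The statement that VLCD loss cannot be adjusted for is wrong in general, and the listed fixed effects leave out the factor on which randomisation is stratified. This should be corrected, but it does not threaten the validity of the trial. A reader might take the omission to bias the treatment effect or to invalidate the sample size. Neither follows: the estimate is unbiased with or without the stratum, and 52 per arm and 140 in total both reproduce.

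The size is that of the table above, from nothing at R2 = 0 to roughly an 8% overstated standard error and 4 points of power at R2 = 0.15. It rests on the assumed R2, a two-sided test, the protocol's SD and correlation, and near-perfect balance within strata. The sponsor stratified because it thought imbalance on this factor mattered, which makes some prognostic value plausible, but nothing in the document measures it.

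**What to change.** Delete the sentence in the Randomization section. In the Statistical analyses section, prespecify the stratum, or VLCD loss as a continuous percentage, in the primary and secondary models, and exempt it from removal by Wald test. For the primary outcome, choose one of two structures and state it:

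- **8-week weight stays a repeated response.** Add stratum and stratum-by-time terms, and do not also use 8-week weight as a covariate.
- **Only weights after randomisation are responses.** Enter 8-week weight and the stratum (or continuous loss) as covariates. This changes the model and should be described as such.

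The cost is a few lines of wording and a few extra model terms. Both weights needed are already collected for every randomised patient.
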